#### Component 1: Qualitative interviews.

We will use an iterative coding process, where initial stakeholder interviews develop the coding scheme, which will be refined as saturation is reached. Subsequent transcripts will be compared to ensure consistent code assignment. As new concepts emerge, the coding structure will be adapted. Grounded theory principles will guide iterative data collection and analysis, with interviews evolving based on emerging themes. Constant comparative analysis will be employed for coding and theme development, and memo writing will follow each interview. The research team will review initial codes, select core categories at data saturation, and complete advanced theoretical coding to ensure logical and comprehensive analysis [114]. After the team has reviewed the coding structure and all interviews have been reviewed in depth by two researchers, trained project staff will independently code all transcripts using the final coding scheme. Twenty percent of the transcripts will be double coded to assess inter-coder agreement. Any differences in coding will be discussed and resolved after discussion with the investigators. Data will be entered into a qualitative software program (Dedoose) [115] to facilitate organization and retrieval. We also will create an analysis audit trail to document all analytic decisions. Targeted analyses will examine the consistency of the data across groups of interviewees. When coding is complete, the team will meet to review summaries of the qualitative results and refine hypotheses about the factors affecting use of the QM2 study.

*Qualitative Analysis:* The semi-structured interviews will be transcribed and analyzed using directed content analysis to identify key facilitators, barriers, and experiences related to the performance coaching intervention [116,117].

Data will be managed using Dedoose software, with field notes taken immediately after each interview. Initial interviews will help develop the coding scheme, and subsequent transcripts will be compared to ensure consistency. As new concepts emerge, the coding structure will be adjusted. Data collection and analysis will be iterative, with interviews modified to reflect emerging themes. After reviewing the coding structure for logical consistency, two researchers will thoroughly examine all interviews before trained project staff independently code all transcripts. To assess inter-coder agreement, 20% of transcripts will be double-coded. Any coding discrepancies will be discussed and resolved with the investigators. An analysis audit trail will be created to document all analytic decisions. Targeted analyses will assess data consistency within sites and identify themes distinguishing high and low-performing clinics. Once coding is complete, the team will review qualitative summaries and refine hypotheses regarding factors and strategies that contribute to successful outcomes or present barriers. For the quantitative survey results, group means and standard deviations will be calculated.

#### Component 2: Survey data.

We will examine within interview period (i.e., cross sectional) and across time (i.e., longitudinal) variation in provider behavioral and environmental influences. Survey data will be linked to the administrative data described above so that we can model clinic variation while adjusting for clinic, client, and community characteristics. We will begin by looking at within interview period descriptive data to examine variation across clinics across survey measures. We will then apply GLMM to examine the observed variation while adjusting for clinic, client, and community characteristics. The models will take the form $F\left(Y_{ij}\right)=\;\alpha +\;\beta_{j}+\;\beta_{\text{1}}C+\;\beta_{\text{2}}P+\;\beta_{\text{3}}E+\;e_{j}$, where $Y_{ij}$ is the survey measure of interest for clinic *i* at time *j,*
$\beta_{j}$ is a fixed effect for time, C is a matrix of measures for clinic characteristics, P is a matrix of measures for clinic client characteristics, and E is a matrix of measures for community factors. For examination of change in practices and environmental influences over time, we use GLMMs with random effects for clinic to account for repeated observations. The parameter of interest will be $\beta_{j}$.

### Ethics approval

Ethics approvals have been obtained from the Institutional Review Board (IRB) of NYU Langone Health, which is overseeing all participating sites: New York State OASAS, University of Connecticut (UConn Health), and Weill Cornell Medicine (WCM). The IRBs at NYU Langone Health and WCM have determined that the research conducted at WCM does not involve human subjects, thus no reliance agreement exists between these two IRBs. However, there is a reliance agreement in place with OASAS and UConn Health. All participants involved in surveys and interviews will provide written or verbal informed consent. Written consent will be collected for in-person data collection, while verbal consent will be obtained for remote or telephone-based interactions, documented by the study team in a secure tracking system, and witnessed by a second team member when possible. The use of administrative data will not require individual consent, as it will be de-identified and used in accordance with institutional and state data-sharing agreements. Retrospective data will be accessed for research purposes starting October 1, 2025, following clinic recruitment. During data collection and analysis, authors may have access to personally identifiable information. Data use agreements with OASAS ensure compliance with all relevant privacy and confidentiality standards.

### Dissemination

This study will adhere to the NIH Public Access Policy, ensuring public access to the published results of NIH-funded research. The trial has been registered with the ClinicalTrials.gov database (#NCT060823). Data generated from this study will be presented at national or international conferences and published promptly. Any published data presentations will be communicated to participants and other stakeholders involved in the trial. All final peer-reviewed manuscripts resulting from this proposal will be submitted to the digital archive PubMed Central. Additionally, the results of this project will leverage OASAS’s investment in its new QM2 strategy and policy leadership.

### Status and timeline

The stepped-wedge trial is projected to begin in July, 2025. We anticipate completing participant recruitment by October 2025, data collection by December 2026, and expect to have preliminary results available by August 2027.

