We will initiate a stepped wedge randomized controlled trial involving 1) 35 clinics receiving a performance coaching intervention and 2) a treatment as usual (TAU) condition for all clinics not participating in the intervention. Additionally, qualitative interviews with stakeholders and surveys of all 550 outpatient clinics will be conducted at three different points in time (years 1, 3, and 4). We will use administrative data from 2021–2027, including records from the Office of Addiction Services and Supports (OASAS) treatment registry, Medicaid, and vital statistics, to monitor client outcomes. This concurrent mixed-methods study [94] will evaluate the impact of the OASAS QM2 strategy on patient outcomes and statewide stakeholders, focusing on retention in care and adverse events (emergency department visits, hospitalizations, and mortality). Clinics will be randomized to one of five sequences, varying the timing of the intervention between years 2 and 4.

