## Materials and methods

### Project 3 aims: Conduct a stepped-wedge trial that includes two conditions: 1) 35 clinics receiving a performance coaching intervention and 2) a treatment as usual (TAU) condition for all clinics not participating in the intervention to examine the effect of the OTP intervention on THD, retention in care, and adverse events

The SPIRIT checklist was used as a guide for reporting this study protocol (Fig 1). To assess the impact of the OASAS QM2 strategy on care retention and adverse events using a stepped-wedge, mixed-methods design across SUD treatment clinics. Clinics will be recruited to participate in this stepped wedge trial by State partners via email invitations, announcements via State listservs, and announcements at relevant meetings to contact the Project Manager or the Principal Investigators. A total of 35 clinics will be recruited after October 2025. The aim of the intervention is to help clinical staff interpret their quality measures and implement subsequent quality improvement efforts through facilitators. The intervention will be six months long for each clinic and be informed by the i-PARIHS model [95].

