Before the trial begins, clinics receiving the QM2 intervention will be randomized into six cohorts of six-month long interventions over three years. Clinics are randomized to onset of intervention in one of six time periods over the three years of the intervention rollout (years 2–4 of the project) and tracked using administrative data. Administrative data will be used for all clinic clients during each of the seven six-month periods (n ≈ 350/clinic) will be drawn from administrative data. The first six-month period will be a baseline prior to any intervention. Six clinics will be assigned randomly to one of six time periods for onset of intervention. Using administrative data, we will track clients within each clinic over four years, including a pre-intervention six-month baseline period. During the same four-year period, clients in clinics not participating in the stepped-wedge trial will be tracked to better understand changes in outcomes under treatment as usual (TAU) and to compare the outcomes of those clinics with clinics receiving the quality management intervention. We anticipate a final study population of approximately 91,000 individuals per year who are receiving treatment from one of the 571 enrolled outpatient substance use treatment programs. Because this is a stepped-wedge trial, all clinics (and as a result all clients within the clinics) will eventually get the intervention, the randomization will have to do with when the clinic is randomized rather than being assigned to a control or intervention group. Fig 2 illustrates the structure of the stepped-wedge trial.

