*Statistical Analyses of the Proposed Stepped-Wedge Trial:* Analyses will begin with examination variable distributions, appropriate transformations, and patterns for, followed by formal imputation methods if needed [110–112]. We will use Generalized Linear Mixed Models (GLMM) for the stepped-wedge design [106].

*Power Analysis for Primary Outcome Statistical power:* Power estimation for specific outcomes was conducted using PASS 2022 software and Monte Carlo simulation [113]. Sample size and baseline rates (μ) were estimated using administrative data. For 80% power, α = 0.05, ICC = 0.05, and a 5-crossover-point stepped-wedge-RCT with 7 clinics starting at each point, power calculations indicate 80% power to detect a small decrease (RR = 0.93) in adverse events with 35 clinics and 350 clients per clinic per 6-month period (n ≈ 73,500 total observations). This corresponds to a decrease from 0.23 to 0.21 events per 6 months. In racial/ethnic subgroups (10% of clients, n ≈ 35 per site), power remains 80% to detect a modest decrease (OR=0.78), from 0.23 to 0.18.

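### The start, recruitment, step and data-collection statements cannot all hold: July 2025 to December 2026 contains only two or three of the five steps behind the stated power, and the 2027 data span rescues five steps under one reading only

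*Protocol article*

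**What the plan says.** All references are to the protocol article.

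- **Status and timeline:** "The stepped-wedge trial is projected to begin in July, 2025", followed by "We anticipate completing participant recruitment by October 2025, data collection by December 2026, and expect to have preliminary results available by August 2027".
- **Project 3 aims, on recruitment and duration:** "A total of 35 clinics will be recruited after October 2025", and "The intervention will be six months long for each clinic".
- **Project 3 aims, text after Fig 1:** clinics are "randomized to onset of intervention in one of six time periods over the three years of the intervention rollout". Randomisation precedes the start of the trial. There are seven half-year periods, the first a baseline, and clients are tracked for four years.
- **Introduction:** "Clinics will be randomized to one of five sequences, varying the timing of the intervention between years 2 and 4", and "We will use administrative data from 2021–2027". The data specification in the analytic plan repeats the 2021–2027 span.
- **Power analysis:** "a 5-crossover-point stepped-wedge-RCT with 7 clinics starting at each point", with 350 clients per clinic per half-year, ICC 0.05, about 73,500 observations, and 80% power for RR 0.93 from a baseline of 0.23.
- **Data specification:** adverse events are counted over the 12 months after treatment entry.
- **Ethics approval:** retrospective data are accessed from 1 October 2025, once clinics have been recruited.

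**The concern.** In a stepped wedge the information on the intervention effect comes from clinics seen to cross over. Clinics whose step falls after the data end contribute control periods only. The stated power assumes that all five groups of seven clinics are observed crossing, with a further period of data after each step. If the calendar ends earlier, the estimate rests on fewer crossovers and the 80% figure no longer describes the trial.

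The recruitment dates raise a second problem. Clinics recruited after October 2025 cannot have been randomised before a July 2025 start, and recruitment is also said to be complete by October 2025. Which date governs decides whether the wedge fits even the longest data span the article gives.

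**Working it through.** **1. Periods the power calculation needs.** 73,500 / (35 × 350) = 6.0. The powered design is therefore a baseline plus five steps, that is 6 × 6 = 36 months. The seven periods in the methods text would give 35 × 350 × 7 = 85,750 observations, so the power section and the methods text describe different designs.

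**2. Periods the calendar gives.** July 2025 to December 2026 is 18 months, or three half-years.

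| Reading of July 2025 | Steps begun by December 2026 | Clinics crossed over | Clinics never seen under intervention | Observations |
|---|---|---|---|---|
| First step, baseline from earlier records | 3 (Jul 2025, Jan 2026, Jul 2026) | 21 | 14 | 35 × 350 × 4 = 49,000 |
| Baseline period | 2 (Jan 2026, Jul 2026) | 14 | 21 | 35 × 350 × 3 = 36,750 |

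Of the 15 intervention cells (sequence by period) in the five-step design, 6 or 3 are seen, so 60% or 80% are unseen. Of all 30 cells, 20 or 15 are seen, so 33% or 50% are unseen.

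**3. The same check with data to December 2027.** July 2025 to December 2027 is 30 months, exactly five half-years.

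- Five steps, retrospective baseline: July 2025, January 2026, July 2026, January 2027, July 2027. The last period ends December 2027, so this just fits.
- Five steps, baseline from July 2025: 36 months, to June 2028. Does not fit.
- Six steps: 36 or 42 months, to June or December 2028. Does not fit.
- Clients admitted during 2027 do not complete 12 months by December 2027.
- Preliminary results in August 2027 come 26 months after July 2025, when about four half-years have passed.

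**4. Power conditional on a December 2026 cut, 35 trial clinics only.** The model is the Hussey–Hughes cross-sectional stepped wedge with generalised least squares. Assumptions not given in the article: two-sided α, cluster autocorrelation 1, and binary variance at the mean rate.

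- p0 = 0.23; p1 = 0.93 × 0.23 = 0.2139; difference 0.0161.
- Mean rate 0.22195; variance 0.22195 × 0.77805 = 0.1727. Within-cluster part 0.1727 × 0.95 = 0.1641; between-cluster part 0.1727 × 0.05 = 0.0086.
- For each sequence s, D_s holds the period dummies and the intervention indicator, and V = (0.1641/350)·I + 0.0086·J. Var(δ) is the last diagonal element of [Σ 7·D_s′V⁻¹D_s]⁻¹.
- Power = Φ(0.0161/SE − 1.96).

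| Steps observed | SE | Power at RR 0.93 | RR detectable at 80% |
|---|---|---|---|
| 5 (as planned) | 0.00534 | 85% | 0.935 |
| 3 | 0.00663 | 68% | 0.919 |
| 2 | 0.00839 | 48% | 0.898 |

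The full design gives 85% where the article states 80%; the detectable RR of 0.935 is close to its 0.93. An autocorrelation of 0.99 brings the full design to 79%, with 61% and 42% for three and two steps. At 0.95 the values are 59%, 42% and 29%.

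**5. Adding treatment-as-usual clinics.** The analytic plan includes them to estimate the time effects. Taking 550 − 35 = 515 such clinics, and assuming 80 to 350 clients per period in each, three steps give 85–87% and two give 60–62% at autocorrelation 1. At 0.95 they give about 60% and 37–38%.

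**The case against.** The strongest reply is that December 2026 is not stated to be the cut for outcome data. The outcomes come from administrative records, which are said twice to run to 2027, and five steps from July 2025 with a retrospective baseline then fit exactly. This stands. A reader might infer that most of the powered wedge will never be observed. The article does not support that: it depends on the December 2026 cut, and even then it is true of intervention cells (60–80% unseen) but not of all cells (33–50% unseen).

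Two further inferences also go too far. One is that only clients with a completed 12-month window count, so that at most one step is usable. No such exclusion is written, and the model allows an offset for time at risk. The other is that the first step falls in January 2026, putting the fifth in January 2028. No passage gives that date.

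The power loss in the 35-clinic table is also not the loss under the planned analysis, because treatment-as-usual clinics recover part of it. That stands too.

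Reading data collection as surveys and interviews only does not remove the conflict. Interviews fall at the end of each clinic's six-month intervention and the staff survey six months after it. With a July 2025 first step, the fifth group finishes its intervention in December 2027.

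Finally, the dates are worded as projections, and the two design figures are not shown and may contain a schedule. So a schedule cannot be called absent. The statements in the text still contradict one another.

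**Conclusion.** The statements conflict and the text is wrong as written. An 18-month calendar cannot contain five or six half-year steps. Clinics recruited after October 2025 cannot be randomised before a July 2025 start. The power section and the methods text disagree on the number of steps.

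The size depends on the true data cut:

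- **Cut at December 2026:** 14 to 21 of 35 clinics are never observed under intervention. Power at RR 0.93 falls from about 85% to about 68% or 48%, for the trial clinics alone with autocorrelation 1. It is about 86% or 62% with treatment-as-usual clinics of assumed size, and lower in either case if autocorrelation is below 1.
- **Cut at December 2027:** five steps fit under one reading only (July 2025 first step, retrospective baseline), and that reading contradicts the later recruitment date. Six steps do not fit, and clients admitted in 2027 have incomplete 12-month outcomes.

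The calendar contradiction rests on the article's own dates and counts. The power values are approximate and rest on the assumptions listed with them.

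**What to change.** Settle on one number of steps and give dates for the baseline, each step start and the administrative data cut. Bring the Introduction, the Project 3 aims, the power analysis, the ethics section and the status paragraph into line with it, including one recruitment date that precedes randomisation.

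Set the data cut at the end of the last step period plus the 12-month outcome window. As an illustration from the article's own start date, five steps beginning July 2025 end in December 2027, so the cut would be December 2028. If the cut cannot move, restate the number of crossovers observed, the total observations and the detectable RR for the truncated wedge. Do this under the planned model, with the treatment-as-usual clinics and the autocorrelation assumption stated.

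The cost is a later data pull and later results than August 2027, or a less favourable stated power. No additional clinics are needed.

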## Conclusion

Quality measurement and improvement in OUD treatment are impeded by several obstacles, particularly in resource-constrained environments. These challenges include insufficient technological capacity due to limited funding, a lack of validated quality measures for specialty SUD treatment, workforce difficulties in data management resulting from inadequate training resources, and concerns from clinic leadership about the fairness of performance assessments that fail to consider the clinical complexity of their clients. To address these challenges, this study will implement the QM2 intervention, which aims to provide performance feedback to clinic leadership and staff to encourage practice improvements and to publicize quality measures for public accountability. The intervention will develop and utilize risk-adjusted quality measures that consider the clinical complexity of clients, thereby ensuring a fair evaluation of clinic performance. By tackling these barriers, the QM2 intervention seeks to promote person-centered care and contribute to the growing body of literature on effective quality improvement strategies in SUD treatment.
